#### *Ethical Considerations for Individual Interviews with Venue Patrons and Workers*

The individual interview does ask questions about the participant's own sexual behavior. Because sites where patron, worker, MSM and transgender women participation is requested are public, the interviewer will ask that he or she move to a different location within or outside the site in order to preserve privacy for the interview. The interviewer will seek a location where no one can visually observe the responses as they are recorded or can overhear the questions and responses. No identifying information will be collected, and written informed consent using initials or an X will be requested in order to preserve privacy to the greatest extent. To protect confidentiality and reduce social desirability bias where the participant responds to questions with an answer he or she thinks is the correct or safe behavior, a number of questions regarding sensitive information could be completed by the participant on their own. If the participant is comfortable responding on the smartphone, the interviewer will ask for the participant to record their responses on the smartphone rather than tell the answers to the interviewer. The pros and cons of self-administered questions vs. interview administered questions will be assessed in the mapping readiness assessment given that in some cultures people may trust an interviewer more than they would an electronic device. Safety and literacy can also influence the feasibility of asking participant to respond on the devices.

For the HIV testing and counseling portion of the study, participants will be asked to enter a private area where their identity cannot be observed and where they cannot be overheard. In some districts this may be a vehicle outfitted with testing kits and supplies, and in others it may be possible to occupy a room or office nearby a cluster of sites where the participant can go for private testing and counseling. After post-test counseling, the participant may be given paper materials about HIV, HIV prevention and contact information for HIV/AIDS treatment and support providers. All participants regardless of their test results will receive the same information.

Because the interviewers will be residents of the areas where the survey is conducted, it will be important that respondents be interviewed by someone unknown to them. Not only does this protect the privacy of the respondent, but it also can prevent coercion. Interviewers will be instructed to not collect survey responses from potential patrons or workers at venues, or participants in the RDS study, with whom they are already acquainted.

The manager or owner of a site will give permission for interviews and HIV testing of workers to occur at the site. This may exert undue influence over workers to agree to consent to the study. In order to minimize the risk of coercion, interviewers will offer to talk to workers who do not want to participate for a period of time equal to the duration of the interview and testing process, so that the manager or owner of the site does not know whether a worker participated or not.

#### *Consent Process for Individual Interviews with Venue Patrons and Workers*

Interviewers will explain to site patrons and workers the purpose of the study, type of questions asked, and that minimal information will be collected from them. The interviewer will review an informed consent statement that describes risks and benefits of participating in the interview, HIV and STI testing, along with the procedure. Subjects will initial or write an "X" on the consent form acknowledging their consent to participate. They will then be provided a copy of the consent form to keep (Appendix 9).

Site patrons and workers, MSM and transgender women will be required to provide written consent by initialing or marking an "X" on the consent document. This mode of consent avoids excluding the significant portion of the potential subject pool that is not be able to sign their name and diminishes the social, psychological, and economic risks to participants should a breach of confidentiality occur, as initials would be more difficult to definitively link to a given subject. We do not collect subject names on the survey questionnaire itself, in order to protect participant confidentiality/privacy given the sensitive nature of some of the questions regarding individual sexual and drug use behavior.

Subjects aged 15-17 who wish to participate in the study will be allowed them to provide independent consent which would be documented with their initialing or marking an X on a written consent form. Subjects age 15-17 will be asked if at the time of the interview, they are accompanied by their parents or if they are running an errand for their parents. Only minors who are not accompanied or running an errand will be asked to participate. Participation in the study may facilitate access to the crucial service of HIV testing for adolescents who may face greater stigma or embarrassment requesting testing at other clinics. Adolescents aged 15-17 have been included in many previous PLACE studies, as they are often among those at highest risk for HIV and other sexually transmitted infections. Furthermore, most of the adolescents eligible for this study will have been identified by nature of visiting a venue where people go to meet sexual partners.

A separate consent will be requested for storage of dried blood spots and unused urine, vaginal swab specimen and/or plasma (Appendix 10). Participants may participate in the survey and not consent to storage of specimens. However, people approached that do not consent to HIV testing will not be eligible for participation.

### Incentives

Participants recruited through the PLACE methodology will not be given an incentive. Participants will not have to spend pocket money on transportation and will benefit from onsite HIV and STI testing.

### Step 5: Feedback and data use

If electronic data collection tools are used, data will be entered and cleaned during field work. If paper data collection forms are used, following field work data entry will be completed in Angola. Data analysis will subsequently be conducted by both the implementing partner in Angola and UNC. Stakeholders in HIV/AIDS prevention and control activities in each province will be invited to participate in a workshop presentation of the results and to discuss the priority action plan based on the sites / people at risk identified. A data use workshop will be conducted to train Ministry of Health and other organization implementing HIV prevention programs for key populations in programmatic planning based on mapping and survey data.

### Risk assessment and collection of biologic specimens

All participants will be tested for HIV using a rapid test and finger prick at or near the recruitment venue. Based on the behavioral questionnaire described above, participants that have sold sex, identify as transgender or are men who have had sex with another man in the past 12 months will be offered additional STI testing for syphilis, Hepatitis B, gonorrhea, chlamydia and trichomoniasis. Participants that meet the definition for key population will be tested for syphilis and Hepatitis B using a rapid test and finger prick at or near the recruitment venue. Participants that test positive for syphilis with a rapid treponemal test will be offered a confirmatory test, which will be conducted at the study laboratory. Participants will be given a phone number and instructions about where and when to collect their results.

The types of tests and specimens performed on participants from the different populations are outlined in Table 1. Briefly, after consent and completion of the behavioral interview, trained counselors will provide HIV and STI pre-test counseling in a private setting. The nurse or lab technician will instruct participants how to collect vaginal swabs, urine samples and anal swabs. Among female sex workers a vaginal swab, among male key populations first-catch urine and anal swabs will be collected to test for *Neisseria gonorrhoeae*, *Chlamydia trachomatis* testing and *Trichomonas vaginalis*. Samples will be immediately stored according to the laboratory procedures manual.

**Table 1 HIV and STI testing schematic by population approached at venues and defined in behavioral questionnaire**

| Population                | HIV rapid test | Syphilis rapid test | Hepatitis B rapid test | Vaginal swab | Urine specimen | Anal swab | CD4 rapid test | Venous blood |
|---------------------------|----------------|---------------------|------------------------|--------------|----------------|-----------|----------------|--------------|
| Female sex workers        | X              | X                   | X                      | X            |                |           |                |              |
| Male sex workers          | X              | X                   | X                      |              | X              | X         |                |              |
| Men who have sex with men | X              | X                   | X                      |              | X              | X         |                |              |
| Transgender women         | X              | X                   | X                      |              | X              | X         |                |              |
| General population        | X              |                     |                        |              |                |           |                |              |
| HIV /syphilis positive    |                |                     |                        |              |                |           | X              | X            |

The justification for the collection of anal swabs is that there have been increases in anal gonorrhea, chlamydia, including strains that cause Lymphogranuloma venereum (LGV) among men who have sex with men in various countries.

A nurse or laboratory personnel will conduct rapid HIV tests with the Determine HIV 1/2 test (Alere/Abbott Laboratories, Waltham, MA, USA) using whole blood obtained by finger prick. A negative test will be considered as a true negative, and the result will be reported to the patient after post-test counseling. A positive test will be confirmed by the Uni-gold HIV test (Trinity Biotech, Bray, Ireland). It is estimated that the HIV test results for the rapid tests will be available after 20 to 30 minutes. Results will be recorded on a HIV test results form.

If the Uni-gold test is positive, the result will be communicated to the participant as a positive result during post-test counseling. The participant will be advised that all positive results with rapid tests will be confirmed by viral load testing at the study laboratory. If results are indeterminate (initial test positive and confirming test negative) a third test will be done for confirmation from the blood already collected. The participant will be counseled about the result and the importance of obtaining follow up, and provided a reference card with his or her code number to obtain the results from the viral load test at the study laboratory in two weeks. The counselor will also advise participants on the recommended referral options for following up HIV and notification of sex partners.

Biologic samples will be stored appropriately as specified in the laboratory standard operating procedures (SOPs).

Female participants that meet the definition for female sex worker will be given a flocked swab from the Xpert CT/NG Vaginal Specimen Collection Kit and asked to collect a vaginal swab specimen in the venue restroom. The participant will return the swab to study staff who will then insert the swab into the Xpert CT/NG collection tube, break off the swab stick at the top of the tube and screw on the top. Study staff will label the tube with the participants ID sticker and note the type of specimen and the date and time of specimen collection. The Xpert CT/NG Specimen Collection Kit is designed to collect, preserve and transport specimens from symptomatic and asymptomatic individuals prior to analysis with the Cepheid Xpert CT/NG Assay. When the study team completes data collection for that day, swab specimens will be transported to the laboratory for testing on the Gene Xpert Instrument Systems. Swab samples in Xpert CT/NG Swab Transport Reagent tubes are stable up to 60 days at 2 °C to 30 °C before testing with the Xpert CT/ NG Assay.

Male participants who meet the definition for MSM or transgender women will be asked to provide first-catch urine (approximately 50 to 60 mL of the initial urine stream) into a urine collection cup free of any preservatives. Collection cups will be marked at the level of 50 mL using a permanent marker (all the way around the cup) to guide participants, however, field staff will instruct participants not to discard urine if the volume exceeds the marked line. Urine collection cups will be labeled with the patient ID sticker and study staff will note the date and time of specimen collection on the cup. At the end of data collection for a given day, all urine specimens will be transported to the study laboratory.

Men who have sex with men and transgender women intercourse will be instructed on collection of an anal specimen using a Xpert CT/NG Specimen Collection Kit designed to collect, preserve and transport patient *Chlamydia trachomatis* and *Neisseria gonorrhoeae* DNA in specimens from symptomatic and asymptomatic

individuals prior to analysis with the Cepheid Xpert CT/NG Assay. Anal specimens are collected from patients using flocked swabs included in the kit. Swabs are broken off into the transport reagent tubes to elute organisms and stabilize DNA. Study staff will label the tube the participant ID sticker and note the date and time of specimen collection on the tube. When the study team finishes data collection for the day, swab specimens will be transported to the laboratory for testing on the Gene Xpert Instrument System. Anal swab specimens will be stored at 2-30 °C and processed within 15 days.

Among HIV positive participants, nurses or lab technicians will collect additional finger prick blood for the rapid CD4 analysis. CD4 testing will be conducted on site using a PIMA CD4 analyzer (Alere, Waltman, MA). The CD4 test takes approximately 20 minutes for processing. Participants will be given the result of their CD4 test by a trained counselor.

Additionally, the laboratory personnel will take a 10 ml sample of venous blood from participants who test positive for HIV and a set of dried blood spots for posterior viral load testing. Whole blood should be collected in EDTA, EDTA-PPT, or ACD collection tubes and will be centrifuged at the study laboratory to separate the plasma and red blood cells per the manufacturer's instructions. A minimum of 1 mL plasma is required for the Xpert HIV-1 Viral Load Assay. Whole blood will be centrifuged and plasma will be stored at 2-8 °C for up to 6 days, prior to testing. Alternatively plasma specimens are stable frozen at  $\leq -18$  °C.

Any pregnant women (regardless of HIV status) receive a rapid syphilis test in order to ensure quick identification and treatment of syphilis-infected pregnant women to prevent congenital syphilis. The nurse will ensure pregnant women with positive rapid syphilis tests receive immediate IM benzathine penicillin G, and treated pregnant women will be referred to a health center once per week for two additional weeks for therapy. Other serum samples including VDRL or RPR will be done for pregnant women as for other participants.

The nurse will refer any person reporting genital ulcers, men reporting urethral or rectal discharge or women reporting vaginal discharge for STI treatment at local health center. The nurse will also provide vouchers for partners (as many as requested by participant) to access free care and treatment at the clinic, NGO or other nearby clinical facility.

Finally, the nurse or counselor will provide a "Results Card" (Appendix X) with a participant number (that will be linked to interview and lab results) and will explain to the participant how they can use this card and get final results of the STI tests taken that day, along with free treatment if any of the results are positive. Participants may choose to refuse collection of one or several of the specimens listed here. Table 2 presents the types of biological specimens and the location where processing will occur.

Table 2 Specimens and laboratory tests

| Specimen                | Test                                                                                                             | Laboratory               | Volume                                                      |
|-------------------------|------------------------------------------------------------------------------------------------------------------|--------------------------|-------------------------------------------------------------|
| Whole Blood             | Determine and Unigold HIV rapid tests                                                                            | Study venue              | Finger prick                                                |
| Whole Blood             | CD4 count, PIMA Analyzer                                                                                         | Study venue              | Finger prick                                                |
| Whole Blood             | Dried Blood Spots for future analysis                                                                            | Study venue              | Finger prick                                                |
| Whole Blood             | Determine TP rapid syphilis test                                                                                 | Study venue              | Finger prick                                                |
| Whole Blood             | Determine HBsAg rapid Hepatitis B test                                                                           | Study venue              | Finger prick                                                |
| Serum                   | RPR or VDRL for syphilis                                                                                         | Study Laboratory, Luanda | 10 ml whole blood in EDTA, EDTA-PPT, or ACD collection tube |
| Serum                   | Xpert Viral load test                                                                                            | Study Laboratory, Luanda |                                                             |
| Vaginal swab from women | Xpert CT/NG ( C. trachomatis / N. gonorrhoeae )
Xpert TV ( Trichomonas vaginalis )       | Study Laboratory, Luanda | Swab                                                        |
| Urine from men          | Xpert CT/NG ( C. trachomatis / N. gonorrhoeae )
Xpert TV ( Trichomonas vaginalis ) n=100 | Study Laboratory, Luanda | 20 ml                                                       |
| Anal swab from men      | Xpert CT/NG ( C. trachomatis / N. gonorrhoeae )                                                    | Study Laboratory, Luanda | Swab                                                        |

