#### *Inclusion Criteria for PLACE*

Male and female participants who meet the following eligibility criteria will be invited to participate in the project:

- At least 15 years of age at time of interview and not accompanying or running an errand for parents
- Recruited at selected venues
- Consent to participant in a face-to-face structured behavioral survey and provide written informed consent with initials or an X

Additionally participants that meet one of the following inclusion criteria for key populations will be offered additional STI testing:

- At least one sexual contact for cash in the last 12 months
- Man or transgender woman that has had oral or anal sex with another man in the past 12 months
- Identification as a male-to-female transgender woman

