Finger-prick blood samples will be collected to measure the CD4 T-cell count of HIV-positive participants using a rapid CD4 T-cell count analyzer, such as the PIMA Analyzer (Alere, Waltham, MA, USA). Based on the results of the CD4 test, patients will be referred to appropriate ART clinics for medical care and treatment. Venous blood will be collected from HIV positive consenting participants for posterior viral load quantification using Xpert Viral Load or PCR. Dried blood spots (DBS) will be collected for all consented participants. Samples will be collected by trained project staff. Participants will receive a finger stick to obtain blood sample according to the methods described in the Abbott DBS Collection Reference Guide (Abbott Laboratories, Abbott Park, IL, USA). Samples will be transported to a central laboratory site for quantitative viral load assay. All specimens must be processed within seven days of receipt at laboratory. Remaining samples will be stored at the testing laboratories in gas-impermeable zip closure storage bags in an -80C freezer for additional testing, as funding becomes available. Participants will be informed of their viral load results within one month of testing.

Men and women identified as at increased risk based on the interview will be offered additional STI testing. People who have been paid for sex or men who have had sex with other men in the past 12 months will be offered testing for syphilis, hepatitis B, gonorrhea, chlamydia and trichomoniasis. Syphilis and Hepatitis B serologic testing will be conducted using finger stick blood and an onsite rapid test. In addition, women will be asked to provide a self-collected vaginal specimen and men will be asked to provide a urine sample for testing

to detect current gonorrhea and chlamydial and trichomonal infections. Men who have had sex with another man and transgender women will be asked to provide a self-collected anal swab for further testing for chlamydia and gonorrhea at the study laboratory. Patrons or workers will be asked to collect these specimens in a restroom onsite. Interviewers will wait outside the restroom to receive the specimens. Participants will be given a phone number and an ID number with which they can collect the results of viral load, gonorrhea, chlamydia and trichomoniasis testing two weeks after participating.

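### The venue survey promises every pregnant woman a rapid syphilis test, but Table 1 and the testing rules leave the exception out, and no instrument or step shown identifies pregnancy

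*Protocol*

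**What the plan says.** The pregnancy rule stands in Protocol section VI.C, under Risk assessment and collection of biologic specimens, in the text after Table 1: "Any pregnant women (regardless of HIV status) receive a rapid syphilis test in order to ensure quick identification and treatment". The stated aim is to prevent congenital syphilis. Treatment follows: "The nurse will ensure pregnant women with positive rapid syphilis tests receive immediate IM benzathine penicillin G", with referral to a health center for two further weekly doses. Serology is added: "Other serum samples including VDRL or RPR will be done for pregnant women as for other participants".

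Three other places in VI.C say who gets syphilis testing:

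- Inclusion Criteria for PLACE: "Additionally participants that meet one of the following inclusion criteria for key populations will be offered additional STI testing". The criteria are paid sex in the last 12 months, a man or transgender woman with a male partner in that period, and transgender identity.
- Recruitment at venues (Step 4): "People who have been paid for sex or men who have had sex with other men in the past 12 months" are offered syphilis and other STI tests.
- Risk assessment and collection of biologic specimens: "Participants that meet the definition for key population will be tested for syphilis and Hepatitis B using a rapid test".

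Table 1 is titled "HIV and STI testing schematic by population approached at venues and defined in behavioral questionnaire". Its general-population row is marked for the HIV rapid test and nothing else, and it has no pregnancy row or footnote.

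On recording, the text after Table 1 says: "Results will be recorded on a HIV test results form". Section VII.D adds that the identifier codes go on the same record.

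**The concern.** The protocol sets itself a safety duty toward pregnant participants and then does not carry it into the parts that field staff are likely to work from. Women outside the key populations are enrolled by design, because Step 4 approaches some people at random without screening for sex work or same-sex behaviour. Staff who follow Table 1 and Form C as printed would give such a woman an HIV test and no syphilis test, pregnant or not.

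The duty also rests on a fact that no step shown collects. The nurse can apply the pregnancy rule, and the immediate injection that goes with it, only once the pregnancy is known. What is at stake is a missed chance to detect and treat maternal syphilis at the venue.

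**Working it through.** No formula applies to the main point. The check sets the rule beside the text that would have to carry it out.

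**1. Who should get the rapid syphilis test**

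| Place in the Protocol | Basis for the test | Pregnancy mentioned? |
|---|---|---|
| VI.C, text after Table 1 | Any pregnant woman | Yes |
| VI.C, Inclusion Criteria for PLACE | Key-population criteria | No |
| VI.C, Recruitment at venues | Paid for sex, or men with male partners | No |
| VI.C, Risk assessment and collection of biologic specimens | Key-population definition, from the questionnaire | No |
| VI.C, Table 1, general-population row | Syphilis cell blank | No |

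**2. Who falls between them**

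- A pregnant woman who has sold sex gets the rapid test under every line. Only the injection rule depends on her pregnancy being known.
- A pregnant woman who has not sold sex gets the test under the first line alone.

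**3. Whether anything shown would reveal pregnancy**

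- Form C (Appendix 4), items Q1 to Q15 and C1 to C39: no pregnancy item. Section C is also headed for continuation only with key-population members, so as printed it would not reach the women who most need the question.
- Venue recruitment: the screening described is for age.
- Counselling, rapid testing and specimen collection in VI.C: none mentions asking about pregnancy.
- Test-results form: the text names results (VI.C) and identifier codes (VII.D). The form itself is not shown.

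**4. Size of the general-population row**

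Section VI.E gives the Luanda targets: 600 sex workers, 600 men who have sex with men, 200 transgender women and about 600 others.

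600 + 600 + 200 + 600 = 2,000, and 600 / 2,000 = 30%.

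This is an outer bound on the Luanda row. The 600 covers men and women together, and the Protocol gives no sex split, no share pregnant and no expected syphilis reactivity, so the calculation stops there.

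**5. Where the gap does not reach**

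- Cabinda: section VI.D offers syphilis testing to all participants, so access to the test does not depend on pregnancy.
- Estimates: the syphilis indicator in Table 4 is defined within key populations, so testing or missing other women does not change it.

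**The case against.** The strongest reply is that there is no contradiction. The pregnancy rule is specific and sits in the same section as Table 1, and none of the three testing rules says that only key populations are tested. A specific rule that adds a group is an exception. Table 1 is also not exhaustive: it has no column for dried blood spots, although Step 4 collects them from all consenting participants. This stands. A reader might infer that the Protocol bars the test for pregnant women outside the key populations; the wording does not support that.

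A second reply is that the question may be asked in material that is not shown: the national counselling protocol, the laboratory manuals and operating procedures, or the test-results form. This also stands as a limit. The point is about the text shown, and it cannot be said that nobody will ask. A woman may also simply tell the nurse, as the referral rule for ulcers and discharge already supposes.

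A third reply concerns sex workers. It is tempting to infer that their treatment as a whole hangs on pregnancy becoming known by chance. It does not: they are rapid-tested, given same-day results, and referred if positive. What can be lost is the immediate injection.

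These replies narrow the point without removing it. Reading the rule as an exception settles the wording, but an exception triggered by pregnancy still needs a step that finds pregnancy. If an unshown form has that step, Table 1 still omits a test that the text requires.

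**Conclusion.** The point holds for the PLACE venue survey. The Protocol makes an exception for pregnant women that Table 1 omits, the three testing rules do not mention, and no instrument or step shown puts into operation. Pregnant women outside the key populations can go untested, and pregnant sex workers can miss the immediate injection.

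Its size is not known. The 30% row is a ceiling for Luanda that includes men, and reading it as 600 women at risk would be wrong. The consequence is for participant safety. A reader might infer bias in the syphilis prevalence estimates, but the indicator's definition does not support that.

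The conclusion assumes that staff work from Table 1 and Form C as printed and that the unshown forms and procedures do not already ask about pregnancy.

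**What to change.** 1. Add to Table 1 a row or footnote for pregnant women in any population, with the syphilis rapid test marked.
2. Add the same exception, in one clause, to Inclusion Criteria for PLACE, to the STI testing paragraph under Recruitment at venues, and to the opening of Risk assessment and collection of biologic specimens.
3. Have the nurse or tester ask every female participant about pregnancy before testing and record the answer on the test-results form. Adding the item only to Section C of Form C would not do, since that section is headed for key-population members.
4. If the results form or a procedure manual already has the question, cite it in the pregnancy rule in place of step 3.

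The cost is one row or footnote, one clause in three places, and one more sensitive question for each female participant. There would be a few more rapid tests, of a kind already run at venues and already required by the pregnancy rule.
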